## Abstract

**Background:** Acute lower respiratory tract conditions are highly prevalent in paediatrics. Many of these conditions present as consolidations on imaging studies. One of the most common causes is bacterial pneumonia (BP), which requires an accurate diagnosis to implement the best treatment plan. Despite the fact that major guidelines constrain the use of invasive tests, chest X-ray (CXR) or blood tests are still routinely used for the diagnosis. In this regard, the introduction of lung ultrasound (LUS) signified an advancement in reducing the invasiveness of diagnosis. However, there are still situations where distinguishing between different aetiologies remains challenging, especially in the case of atelectasis. **Methods:** This is a prospective cohort study to assess the diagnostic accuracy of new non-invasive, quantifiable, and reproducible imaging biomarkers (lung elastance and microvascularization ratio) for differentiating BP from another major entity that causes the appearance of consolidation in imaging tests, atelectasis. It will be conducted at Sant Joan de Déu Hospital in Spain from June 2025 to June 2027. Firstly, imaging biomarkers will be measured in well-aerated lung tissue without consolidation to establish their values in healthy lung tissue, according to a predefined imaging acquisition protocol. Subsequently, the imaging biomarkers will be assessed in patients with confirmed lung consolidation by LUS (Group 1: BP; Group 2: atelectasis). **Results**: The study aims to determine whether there are statistically significant differences in the biomarker values in relation to the normal values and between the different etiological groups. **Conclusions**: The demonstration of the reliable diagnostic accuracy of these biomarkers could significantly reduce the need for invasive techniques and improve the therapeutic management of many patients with BP and other pulmonary conditions presenting with consolidation in imaging tests.

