### 2.2. Outcomes

Determine normal values for the imaging biomarkers (elastance and microvascularization) in healthy lung parenchyma and within different healthy areas.Determine the values for the imaging biomarkers (elastance and microvascularization) in lung consolidation.Evaluate differences between the imaging biomarker values on healthy lung vs. consolidated lung.Evaluate differences between the imaging biomarker values of group 1 (BP) vs. group 2 (atelectasis). This would allow the establishment of a cut-off point for the etiological differentiation of lung consolidations.

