### 2.7. Statistical Analysis and Sample Size

To determine the normal reference values of elastance and microvascularization ratio in the healthy lung, measures of central tendency (mean and median) and dispersion (standard deviation, interquartile range) will be calculated for both elastance and microvascularization variables. The distribution of the variables will be assessed using the Shapiro–Wilk test to determine if the data follows a normal distribution. If the variables follow a normal distribution, the standard approach will be applied using the Faulkenberry-Weeks approach implemented in the tolerance R package. If the variables deviate from normality, non-parametric bootstrap methods will be used to estimate the tolerance intervals. Variability of the biomarkers across different patient subgroups (e.g., by sex or age) will be explored using analysis of variance (ANOVA), provided the assumptions of ANOVA are met. If assumptions are not met, permutation tests will be applied. A *p*-value of less than 0.05 will be considered statistically significant for all statistical tests. A sample of 60 subjects is considered sufficient to obtain 90% tolerance intervals at 95% confidence with a 5% error in tolerance and a 2.5% error in confidence [30].

Subsequently, to establish differences in the values of the imaging biomarkers among the different groups (BP, atelectasis, and normal baseline), analysis of variance (ANOVA) will be performed. In the event of finding significant differences, post-hoc analysis will be conducted using Tukey’s method. If the conditions for the applicability of ANOVA are not met, a permutation test will be applied. The sample size for the ANOVA test is calculated using the method proposed by Cohen. According to this method, the test effect size is the ratio of the sum of squares between groups to the total sum of squares. Cohen suggested a value of 0.25 as a medium effect size. The sample size is calculated using the pwr R package, which gives a sample size of 53 subjects per group required to detect a medium effect size with 80% power and three groups [31].

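### The stated aim is diagnostic accuracy and a cut-off for bacterial pneumonia versus atelectasis, but the stated analysis and sample size serve only a three-group comparison of means

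*Protocol article*

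**What the plan says.** **Aim.** The Abstract of the protocol article says: "This is a prospective cohort study to assess the diagnostic accuracy of new non-invasive, quantifiable, and reproducible imaging biomarkers". The target is differentiating BP from atelectasis. Its Conclusions look ahead to the same claim: "The demonstration of the reliable diagnostic accuracy of these biomarkers could significantly reduce the need for invasive techniques".

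**Expected result.** The Abstract's Results sentence is worded differently: "The study aims to determine whether there are statistically significant differences in the biomarker values in relation to the normal values", and it continues to differences between the aetiological groups.

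**Cut-off.** Section 2.2 lists four outcomes, all of them biomarker values or differences in values. After the last, BP versus atelectasis, it adds: "This would allow the establishment of a cut-off point for the etiological differentiation of lung consolidations".

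**Analysis.** Section 2.7 gives tolerance intervals for the normal values. For comparing biomarker values "among the different groups (BP, atelectasis, and normal baseline), analysis of variance (ANOVA) will be performed". Then: "In the event of finding significant differences, post-hoc analysis will be conducted using Tukey’s method". A permutation test replaces ANOVA if its assumptions fail. A p-value "of less than 0.05 will be considered statistically significant for all statistical tests".

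**Sample size.** Section 2.7 takes Cohen's medium effect of 0.25, three groups and 80% power, and arrives at 53 per group.

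**The concern.** Accuracy and difference in means are separate questions. A diagnostic-accuracy aim calls for sensitivity, specificity or AUC with their uncertainty, and a cut-off calls for a way of choosing it and judging its performance. ANOVA, Tukey comparisons and permutation tests give a p-value and differences in means. None of them says how well a child with a consolidation would be classified.

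The sample size carries the same mismatch. It is set by the power of an omnibus test that includes a normal-lung group, although the clinical question concerns only the two consolidation groups.

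At stake is the central claim. The Discussion links the biomarkers to fewer empirical antibiotics and less reliance on chest X-ray. A statement about reliable accuracy would need estimates that the stated analysis does not produce.

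**Working it through.** **Inputs.** From Section 2.7: three groups, effect size 0.25, 80% power, significance level 0.05, 53 per group. From the Introduction: adult elasticity of 2.51 ± 1.14 kPa in atelectasis and 19.98 ± 15.59 kPa in pneumonic consolidation. Assumptions for steps 2 to 4: normal data with equal SD, and 53 in each group.

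**1. The plan's own figure.** Power of the one-way F test from the noncentral F distribution, with noncentrality 3·n·f² and f = 0.25:
- n = 52: 79.7%
- n = 53: 80.5%

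So 53 per group reproduces. Section 2.7 describes the effect size as between-group over total sum of squares. Read literally, 0.25 would mean f = √(0.25/0.75) = 0.577 and only 11 per group. The stated 53 therefore rests on f = 0.25.

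**2. What f = 0.25 means for BP versus atelectasis.** Here f is the SD of the three group means (divisor 3) over the within-group SD, and d is the BP-atelectasis gap in SD units. The widest gap has the third mean midway: f² = d²/6, so d = 0.25 × √6 = 0.612. If only BP differs, f² = 2d²/9, so d = 0.25 × 3/√2 = 0.530. Then AUC = Φ(d/√2), and at the midpoint cut-off sensitivity = specificity = Φ(d/2).

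| Pattern of means | d | AUC | Sens = spec | Tukey power for this pair |
|---|---|---|---|---|
| BP and atelectasis at the extremes, normal midway | 0.612 | 0.667 | 62% | 79% |
| BP differs, atelectasis equals normal | 0.530 | 0.646 | 60% | 64% |
| Normal at one extreme, atelectasis midway | 0.306 | 0.586 | 56% | 22% |
| Only normal differs | 0 | 0.500 | 50% | not applicable |

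Tukey power is from 20,000 simulated trials per pattern. All four rows have the same 80.5% power for the omnibus test.

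**3. Smallest observed difference that Tukey would call significant.** The critical studentized range for 3 groups and 156 degrees of freedom is about 3.35, so d = 3.35/√53 = 0.46 and AUC = Φ(0.46/√2) ≈ 0.63.

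**4. Precision of an AUC from 53 versus 53 (Hanley-McNeil).** SE² = [A(1−A) + 52(R₁−A²) + 52(R₂−A²)]/53², with R₁ = A/(2−A) and R₂ = 2A²/(1+A).
- A = 0.80: R₁ = 0.667, R₂ = 0.711, SE = 0.0432, half-width 1.96 × 0.0432 = 0.085, interval 0.715 to 0.885.
- A = 0.90: SE = 0.0312, half-width 0.061, interval 0.839 to 0.961.

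For a sensitivity or specificity from 53 children, 1.96·√[p(1−p)/53] gives ±0.096 at 85% and ±0.081 at 90%.

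**5. The protocol's own effect data.** Allowing unequal SDs, AUC = Φ[(19.98 − 2.51)/√(1.14² + 15.59²)] = Φ(17.47/15.63) = 0.868. A lognormal model gives 0.99. The Introduction says no such data exist for the microvascularization ratio in these lesions.

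**6. If a cut-off were chosen in the same data.** The article does not say how the cut-off will be found. As an illustration, the one that maximises the Youden index at 53 versus 53 (2,000 simulated trials) gives an apparent index of 0.29 to 0.30 against a true 0.20 at d = 0.55, and 0.62 against 0.55 at d = 1.58. The second d is the adult difference over the root mean square of the two SDs, 17.47/11.05.

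**The case against.** **The outcomes are differences.** All four items in Section 2.2 are values or differences, and Section 2.7 addresses them. The cut-off is presented as a consequence, not as an outcome with its own test. This is fair. It moves the mismatch without removing it: the Abstract still names accuracy as the purpose and Section 2.2 still expects a cut-off.

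**A fuller analysis plan may add ROC methods.** It may, and the absence of ROC detail is not the point. Section 2.7 does state an analysis and a sample-size basis, and both answer a different question from the stated aim. A later plan would not change what 53 per group was justified by.

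**The expected effect is large.** The adult elasticity data point well above the sized effect. This stands, and it limits the conclusion. A reader might infer that a significant result here means an AUC of about 0.65, or a marker little better than chance. The documents do not support that: 0.667 is the ceiling at the effect used for sizing, and significance is equally compatible with 0.87. The conversion also assumes equal SDs, whereas the adult SDs differ about 14-fold (15.59/1.14).

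**Other tempting readings.** A reader might infer that the plan equates significance with accuracy. No such rule is stated, and the Abstract's conclusion is conditional. A reader might also set these figures against the 90%/68% for Colour Doppler or the 90%/85% for lung ultrasound plus procalcitonin. The first comes from an adult ICU and the second from a combined strategy, while the Discussion casts the new markers as complementary to ultrasound. Neither is a like-for-like benchmark.

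**Conclusion.** The concern holds as a mismatch between aim and method. The accuracy aim and the expected cut-off are not served by the three-group ANOVA with Tukey, nor by a sample size derived from it. At the sized effect the BP-atelectasis AUC is at most 0.667, and as low as 0.50 if only normal lung differs. The smallest Tukey-significant difference corresponds to about 0.63, while the adult elasticity data suggest about 0.87. One p-value below 0.05 would cover all of these, so it cannot show whether a marker is useful. This matters most for the microvascularization ratio, for which the protocol has no prior effect data.

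The AUC figures for the sized effect rest on normality, equal SDs and 53 per group, and the 0.87 on a binormal model with unequal SDs. The mismatch itself rests only on the text. The number of children need not be wrong: 53 per group gives usable though not tight AUC precision, but the plan does not justify it that way.

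**What to change.** Amend Section 2.7 before Phase 2 data are examined:

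- Make the main BP-versus-atelectasis analysis the AUC with 95% CI, for elastance, for the microvascularization ratio, and for the two combined.
- Report sensitivity and specificity with intervals at the chosen cut-off, with bootstrap optimism correction that repeats the cut-off selection in each resample.
- Keep ANOVA with Tukey, or the permutation test, as supporting analysis.
- State the precision that 53 per group gives: about ±0.085 at an AUC of 0.80 and ±0.061 at 0.90.
- Base any conclusion about accuracy on these estimates and their intervals, not on p < 0.05.

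A minimum AUC that the lower confidence limit must exceed is optional. It is a debatable design choice for markers not yet evaluated in children, and it could require more patients: at 53 per group an observed AUC of 0.80 has a lower limit of only 0.715.

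Without such a threshold the cost is a little more analysis on data already being collected, with no added patients or measurements. The reported accuracy will be less favourable after correction, noticeably so if the separation is weak: the illustration above falls from about 0.30 to 0.20 on the Youden index.

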## 1. Introduction

Acute lower respiratory tract infections are highly prevalent in the paediatric population and represent one of the leading causes of admission to paediatric intensive care units (PICUs) [1]. Specifically, community-acquired pneumonia (CAP) remains one of the primary causes of death among paediatric patients worldwide [2]. The typical symptoms of pneumonia are fever, cough, tachypnoea, and respiratory distress. However, younger children may present with non-specific symptoms such as irritability or refusal to feed [3]. CAP is primarily caused by bacterial or viral infections. Although the diagnosis of CAP generally relies on a combination of clinical signs, blood tests, imaging techniques, and microbiological parameters, the British Thoracic Society (BTS) recommends basing the diagnosis on clinical findings alone, advising against routine use of chest X-rays (CXRs) to reduce radiation exposure. Furthermore, the use of acute phase reactants to differentiate between viral and bacterial infections is discouraged [4]. In the PICU setting, nosocomial pneumonia (NP) due to bacterial infection is particularly common. This category includes both hospital-acquired pneumonia and ventilator-associated pneumonia (VAP) and constitutes one of the main healthcare-associated infections in hospitals [5]. NP should be suspected in any patient who develops a lung infection after 48 h of hospitalization or within the first 7 days following hospital discharge. Focusing on VAP, it develops after 48 h of mechanical ventilation and is identified by the presence of a new infiltrate on CXR, along with positive microbiological findings from the lower respiratory tract and/or two or more positive clinical signs of pneumonia. VAP is a highly prevalent condition, and while there is no single Gold Standard diagnostic tool, the Centers for Disease Control and Prevention (CDC) criteria are the most widely accepted and utilized [6].

Regarding the use of analytical parameters, the British Thoracic Society (BTS) discourages the routine use of acute phase reactants, such as C-reactive protein (CRP) or procalcitonin (PCT), for differentiating between bacterial and viral aetiologies [4]. The Infectious Diseases Society of America (IDSA) recommends using these markers alongside clinical parameters only in patients with severe infections requiring hospitalization or those who develop pneumonia-related complications [7]. Microbiological data can assist in confirming a potential infectious aetiology; however, it is often unavailable during the early stages of diagnosis. Additionally, sputum cultures, blood cultures, and bronchoalveolar lavage exhibit relatively low sensitivity and do not always identify the causative agent [8]. In contrast, recent advancements in PCR technology have enabled the detection of multiple specific respiratory pathogens, including both viruses and bacteria, achieving high diagnostic accuracy [9,10]. Regarding imaging tests, IDSA guidelines recommend performing a CXR with both posteroanterior and lateral projections in all children hospitalized with pneumonia who present hypoxemia or respiratory distress, as well as in cases where initial antibiotic therapy fails [7]. The characteristic radiographic finding of BP is the presence of a consolidation (lobar pattern). However, this is not a pathognomonic feature of BP and may be associated with other non-infectious conditions, the most common of which is atelectasis. Atelectasis is defined as the partial or total collapse of a lung segment, which can result from internal airway obstruction (e.g., due to mucus), extrinsic compression (e.g., from a pleural effusion or pneumothorax), or a loss of surfactant (particularly relevant in premature infants). This condition can impair gas exchange and lead to symptoms similar to those caused by pneumonia, including respiratory distress, cough, and/or chest pain. Less commonly, lung consolidation may be due to pulmonary contusions or pulmonary thromboembolism, although the patient’s clinical context is usually characteristic and facilitates its identification [11].

In recent years, lung ultrasound (LUS) has been increasingly used to enhance the pneumonia diagnosis. LUS is a reliable, rapid, and non-invasive technique that can be performed at the patient’s bedside. Moreover, LUS has reduced radiological exposure associated with the routine use of CXR and has decreased antibiotic exposure [12,13]. In most cases, LUS may allow the distinction between BP and VP. The typical LUS findings of BP are pleural line disruption, a hypoechoic consolidation (>1 cm) with arboriform and dynamic air bronchogram inside, and perilesional B-line enhancement, often associated with pleural effusion (Figure 1a). In contrast, VP is usually seen on LUS as small subpleural consolidations (<1 cm) and accumulation of perilesional B-lines, without air bronchogram (Figure 1b). Atelectasis typically appears on LUS as an area of consolidated tissue (>1 cm) with a static and parallel bronchogram and possible loss of movement of the adjacent pleura (Figure 1c) [14,15,16]. Several publications have demonstrated the high efficacy of LUS in diagnosing these conditions compared to CXR. Yan et al. found that the pooled sensitivity, specificity, and diagnostic odds ratio (DOR) for paediatric pneumonia diagnosed by LUS were 0.95 (95% CI: 0.94 to 0.96), 0.90 (95% CI: 0.87 to 0.92), and 137.49 (95% CI: 60.21 to 313.98), respectively. For CXR, the pooled sensitivity, specificity, and DOR were 0.91 (95% CI: 0.90 to 0.93), 1.00 (95% CI: 0.99 to 1.00), and 369.66 (95% CI: 137.14 to 996.47), respectively. Similarly, several studies have assessed the utility and effectiveness of LUS in diagnosing atelectasis compared to CXR [17]. Martinez-Molina et al. compared both imaging techniques in 100 adult patients and found that LUS demonstrated a sensitivity of 85%, specificity of 100%, positive predictive value of 100%, and negative predictive value of 55% for detecting atelectasis [18].

Given all this, in daily clinical practice, particularly in hospital wards or the PICU, the main difficulty for clinicians lies in the differentiation between BP and atelectasis, due to the similarity of their LUS findings in patients with possible similar clinical features. This is especially relevant in situations where BP has minimal impact and no fever or signs of infection are present during the patient’s physical examination. In contrast, VP is usually well differentiated through LUS and the clinical context, as are other conditions such as contusion or pulmonary thromboembolism, which can also cause lung consolidations but are typically framed within a very specific and characteristic clinical context.

Given the difficulty of LUS in some cases in differentiating between BP and atelectasis, a precise differential diagnosis of these conditions often requires invasive procedures, such as blood draws, which can be particularly challenging in paediatrics. Previous studies, such as the PROLUSP trial, have demonstrated that combining LUS with PCT enhances diagnostic accuracy for BP, achieving 90% sensitivity and 85% specificity [19,20]. Our research group suggests evaluating the usefulness of new, quantitative, non-invasive, and reproducible imaging biomarkers for diagnosing BP and atelectasis, such as lung elastance measured by Shear Wave Elastography (SWE) and the lung microvascular ratio assessed by Superb Microvascular Imaging (SMI). SWE assesses tissue elastance by measuring the propagation speed of shear waves, which originate perpendicularly from the initial acoustic radiation emitted by the transducer as it scans multiple focal areas of the tissue [21,22,23]. SWE is widely used for the liver, breast, prostate, and thyroid, but its application to lung tissue remains limited, despite several research groups suggesting its potential usefulness in this organ [24,25,26,27]. Similarly, the role of microvascularization within a pulmonary consolidation has not been studied to date, so its relevance in the differential diagnosis of various lung consolidations remains unknown. In recent years, technological tools have been developed and improved to allow the visualization of blood flow in microvessels. Specifically, SMI technology can suppress interference and thereby extract the blood flow signal from both large and small vessels, ultimately representing this information as a color-overlay image and translating it into a microvascularization ratio. Its use has been studied mainly in the breast and thyroid, so knowledge of its usefulness in the lung is very scarce [28,29].

Table 1 provides a comparison of the characteristics of the different imaging techniques mentioned, based on their applicability to lung tissue.

Considering that in BP, inflammation and alveolar filling with fluid and immune cells occur, leading to the hepatization of pulmonary tissue, while in atelectasis, there is alveolar collapse with a reduction in lung volume and tissue compression, our research group hypothesizes that BP will exhibit decreased pulmonary elasticity but a higher microvascularization ratio compared to atelectasis. Therefore, both SWE and SMI may play a crucial role in assessing these pathophysiological characteristics, thus contributing to the accurate characterization and diagnosis of these conditions. This hypothesis is supported by several studies conducted in adults. Lim et al. evaluated the elasticity of atelectasis and BP, among other lesions, and reported an elasticity of 2.51 ± 1.14 kPa in atelectasis and 19.98 ± 15.59 kPa in pneumonic consolidations. To date, no studies have been published regarding the microvascularization ratio in these lesions [23].

Up until now, the normal values of these imaging biomarkers and the role of these diagnostic tests have yet to be evaluated in the paediatric population. The ELASMIC study aims to analyze the ability of quantitative lung imaging biomarkers (elastance measured with SWE and microvascularization ratio measured with SMI) to discriminate between BP from other causes of lung consolidation such as atelectasis, reducing the need for invasive and radiation-based diagnostics in the paediatric population. As discussed previously, distinct values of elastance and microvascularization ratio are expected given the pathophysiological differences of each entity. The identification of statistically significant differences in imaging biomarkers between BP and atelectasis could significantly enhance the diagnostic approach to these disorders, offering a less invasive method and enabling a more precise quantitative characterization of the underlying pathological processes.

